**Summary**

Protocol title: Internet Based Transdiagnostic Treatment for Anxiety - A Randomised Controlled Trial of the Anxiety Program

Protocol version: 2

Objectives Primary objective: To explore the outcomes of the Anxiety program for participants with either Generalised Anxiety Disorder (GAD), social phobia, or panic disorder (with or without agoraphobia), who receive clinician assisted computerized cognitive behavioural therapy (CaCCBT), against participants who receive computerized CBT with reminder calls from administrative staff (CCBT), against participants who remain on the wait list, using a randomized controlled trial design.

Secondary objectives: To further determine the feasibility of these treatments in terms of acceptability to patients and practicality for clinicians.

Study design: A CONSORT-R compliant, registered RCT of the intervention (CaCCBT) versus CCBT versus waitlist control group.

Planned sample size: 150

Selection criteria: Meets criteria for GAD, social phobia, or panic disorder (with or without agoraphobia) as a primary diagnosis.

Study procedure Recruit and treat subjects with GAD, social phobia or panic disorder (with or without agoraphobia)

Statistical considerations: Sample size calculation: Assuming ES > 0.5

Analysis plan: ANCOVA of post-treatment scores on measures of depression, anxiety, disability, and treatment satisfaction, while controlling for pre-treatment score. T-tests and *X*^2^ on pre-treatment scores to determine equivalence between groups.

Duration of the Study: 18 months

TABLE OF CONTENTs PAGE

1. BACKGROUND 6

1.1 Disease Background 6

1.2 Rationale for Performing the Study 7

2. STUDY OBJECTIVES 7

2.1 Primary Objective 7

2.2 Secondary objectives 8

3. STUDY DESIGN 7

3.1 Design 7

3.2 Study Groups 8

3.3 Number of Participants 8

3.4 Number of Centres 8

3.5 Duration 8

4. PARTICIPANT SELECTION 8

4.1 Inclusion Criteria 8

4.2 Exclusion Criteria 8

5. STUDY OUTLINE 9

5.1 Study Flow Chart 9

5.2 Investigation Plan 10

5.3 Study Procedure Risks 12

5.4 Recruitment and Screening 12

5.5 Informed Consent Process 12

5.6 Enrolment Procedure 12

5.7 Randomisation Procedure 12

6. SAFETY 12

6.1 Adverse Event Reporting 12

6.2 Serious Adverse Event Reporting 13

6.3 Data Safety and Monitoring Board - membership and responsibilities 13

6.4 References to national and international guidelines on research in humans 13

6.5 Early Study Termination 13

7. BLINIDING AND UNBLINDING 13

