## Number of participants

150 in total: CaCCBT: n=50; CCBT: n = 50; Waitlist: n= 50

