# STATISTICAL CONSIDERATIONS

## Sample Size Calculation

We would expect pre-post improvement of ES 1.0 for the CaCCBT groups on Anxiety Disorder measures. We also expect the CaCCBT group to improve more than the CCBT group by an ES of 0.3 and waitlist group by an ES of 0.6. Sample size is powered to have an 80% chance of detecting differences at p<.05.

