## Analysis Plan

Analyses based on completers and on intention to treat will be performed. Three mixed design ANCOVAs will be carried out utilising SPSS GLM with the baseline score entered as a covariate. The within subject factor examines the difference in pre-post scores for each of the three treatment conditions, whilst the between subjects factor compares improvement scores between treatment groups.

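### The baseline t-tests and chi-square tests cannot determine equivalence between the arms; a descriptive baseline table should replace them

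*Protocol*

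**What the plan says.** The Summary's analysis plan has two parts. The first is an ANCOVA of post-treatment scores "while controlling for pre-treatment score". The second is a set of t-tests and chi-square tests "on pre-treatment scores to determine equivalence between groups". No margin is given for what would count as equivalent at baseline.

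The Analysis Plan section repeats the covariate (the ANCOVAs are run "with the baseline score entered as a covariate") and does not mention baseline tests. It names no covariate other than the baseline score.

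The arm sizes are "CaCCBT: n=50; CCBT: n = 50; Waitlist: n= 50". The Sample Size Calculation section expects the CaCCBT group to "improve more than the CCBT group by an ES of 0.3 and waitlist group by an ES of 0.6".

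The Enrolment and Randomization procedure sections place allocation before the telephone interview, and the flow chart places randomisation before the pre-treatment assessment.

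**The concern.** The sentence gives the tests a job they cannot do. A t-test or chi-square test takes no difference as its null hypothesis. Failure to reject may mean that the groups are alike, or only that the sample is too small to tell. To determine equivalence, one must state a margin and show that the difference lies inside it; the protocol does neither.

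At stake is a reported claim that the arms were equivalent before treatment, made when they may differ by more than the smallest effect the trial expects. The order of events makes this more than a matter of wording. Because allocation comes before the interview that confirms the diagnosis, exclusions after allocation could make the arms differ for reasons other than chance. A non-significant p-value read as equivalence could cover such a difference.

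**Working it through.** **Inputs.** 50 per arm (Number of participants); expected effect size 0.3 for CaCCBT against CCBT and two-sided use of the 5% level (Sample Size Calculation; sidedness is not stated, so two-sided is assumed). Effect sizes are read as SD units, which the protocol does not spell out. The calculation is for one pair of arms.

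**1. The plan's own figure.** The sentence on baseline tests contains no number. The only related figure is the sample size. With n per arm = 2(z₁₋α + z₀.₈₀)² / ES², an effect size of 0.5 ("Sample size calculation: Assuming ES > 0.5") and a one-sided 5% level:

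2 × (1.645 + 0.842)² / 0.25 = 49.5, so 50 per arm and 150 in total.

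This matches the stated total, though a two-sided test would need 63 per arm. It confirms 50 per arm as the size to work with and does not otherwise bear on this point.

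**2. Largest observed difference that stays non-significant.**

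- Standard error of a difference in means, in SD units: √(2/50) = 0.20.
- Critical value of t with 98 degrees of freedom, two-sided 5%: 1.984.
- Threshold: 1.984 × 0.20 = 0.397, about 0.40 SD.

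Any smaller observed difference gives p > .05.

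**3. An observed difference equal to the expected effect.** For 0.3 SD, t = 0.3 / 0.20 = 1.5, and p is about 0.14. The test would pass an imbalance as large as the CaCCBT–CCBT effect being sought.

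**4. What the data could show at best.** The 95% confidence interval for a baseline difference has half-width 0.40 SD. Even an observed difference of exactly zero would leave differences of 0.3 SD in either direction inside the interval. Take 0.3 as an illustrative margin (the protocol gives none) and use the usual pair of one-sided 5% tests. The relevant 90% interval has half-width 1.661 × 0.20 = 0.33 SD, still wider than the margin. With 50 per arm, equivalence to within 0.3 SD could not be shown whatever was observed.

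**5. How far this reaches the outcome comparison.** Without adjustment, a baseline imbalance of 0.3 SD would shift the post-treatment difference by r × 0.3, where r is the pre–post correlation. The protocol gives no r. For an assumed range of 0.4 to 0.7 the shift is 0.4 × 0.3 = 0.12 SD to 0.7 × 0.3 = 0.21 SD. The planned ANCOVA removes this for the scale's own baseline, whatever the baseline tests show.

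**The case against.** The strongest reply is that this is one loosely worded line in a summary. The model is fixed elsewhere: the baseline score is a covariate in both the Summary and the Analysis Plan, so an imbalance on a scale's own baseline is adjusted for regardless. Comparing the arms at baseline also has a real purpose here, since exclusions could follow allocation in an unblinded study. All of this stands. It limits the consequence, but it does not make the tests capable of showing equivalence. The legitimate purpose is better served by a descriptive table with exclusions by arm.

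Several stronger readings are tempting and are not supported:

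- **That covariates will be chosen from the test results, or that the primary conclusion rests on them.** No section says so. The baseline-score covariate is already prespecified.
- **That the tests would flag trivial imbalances.** With 50 per arm, anything flagged is at least about 0.40 SD.
- **That a significant result could only be chance.** This holds if randomisation is intact through to the baseline assessment. Here the diagnostic interview and the pre-treatment assessment both come after allocation.
- **That some 33 tests will be run (11 questionnaires by 3 pairs of arms), with false positives to match.** The protocol does not say which scales or which pairs will be tested, so any such count is an assumption.
- **That leaving out primary diagnosis is an error.** Further covariates may be listed in an analysis plan that is not shown. Hypothesis 2 already compares participants with controls who share the same primary diagnosis. Adding diagnosis is an improvement to the model rather than the correction of a mistake.

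**Conclusion.** The point holds as a minor one. The Summary states an analysis that cannot deliver its stated conclusion: observed baseline differences up to about 0.40 SD would count as equivalence, against an expected CaCCBT–CCBT effect of 0.3. This rests on 50 analysed per arm, a two-sided 5% t-test for one pair of arms, and effect sizes in SD units. With fewer than 50 per arm at baseline, the threshold would be larger. The same logic applies to the chi-square tests, but they are not quantified because the protocol does not name the categorical variables.

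The likely harm is an unsupported statement in the report rather than a wrong primary estimate. Sample size is unaffected.

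**What to change.** Remove the t-tests and chi-square tests on pre-treatment scores from the Summary, along with the claim that they determine equivalence. Replace them with text along these lines:

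*Baseline characteristics and pre-treatment scores will be summarised by arm with means and SDs, or counts and percentages, without significance tests. The numbers allocated, and those excluded after allocation with reasons, will be reported by arm.*

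Keep the prespecified ANCOVA on the baseline score. In the comparisons that use all participants, add primary diagnosis (GAD, social phobia, panic disorder) as a fixed covariate, whatever imbalance is observed. The same statement should appear in the Summary and the Analysis Plan.

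**Cost.** No new data and no change to the total of 150: primary diagnosis is already collected at the interview and is needed for hypothesis 2. The first change is wording only. The second alters the model: a three-level factor uses two degrees of freedom, so with all 150 analysed the residual falls from 150 − 3 − 1 = 146 to 144, which is negligible. Because the interview follows allocation in an unblinded study, primary diagnosis should be recorded by the same procedure in all three arms.

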# BACKGROUND

## Disease Background

There is increasing evidence that anxiety and depression share a common etiology. Goldberg et al, (in press), points to a number of shared characteristics including heritability, familiality, course, response to treatment and vulnerabilities between the disorders as evidence that what the disorders have in common outweighs what they do not.

This approach has sparked interest in the field of treatment for these disorders. The approach of treating what is common between disorders, often referred to as transdiagnostic treatment, has received growing attention (e.g. Page & Hooke, 2003; Lumpkin et al, 2002; Norton, 2008). Recent meta analyses of transdiagnostic treatment for the anxiety disorders (Norton & Price, 2007), and for anxiety combined with depression (McEvoy et al, 2009), has supported the efficacy of this approach, suggesting equivalence between disorder-specific and transdiagnostic treatments for the common mental disorders.

Despite the existence of effective disorder specific and transdiagnostic treatments, nearly two thirds of people with a mental disorder do not seek help, and only 22% of people with an anxiety disorder utilized a mental health service (ABS, 2009). The reason for the shortfall is well known as being a mixture of societal, attitudinal and diagnostic variables (Andrews et al, 2001). Making treatment more freely available in areas where expert treatment is not available, or to people who are unable to take time off work to access treatment is one logical step to improving access to effective healthcare.

We recently completed randomised controlled trials of clinician assisted computerised cognitive behavioural therapy (CaCCBT) for the distance treatment of people with social phobia (Titov et al, 2008a), GAD (Titov et al, 2009a), and panic disorder (Wims et al, 2008). Adherence across all the studies was good (social phobia, 80%; GAD, 75%, panic disorder 88%). Patients in the intervention groups were severe and yet made significant improvement (social phobia, ES=1.2 ; GAD, ES=1.3; Panic, ES=1.0). This level of improvement is roughly equivalent to that seen in our face-to-face anxiety disorders clinic at St Vincent’s hospital. However, the CaCCBT groups only required roughly one quarter as much clinician time as usual face to face treatment. This finding has been replicated for the social phobia program (Titov et al, 2008b), and replication studies for the GAD and depression programs will be finalised by the end of the year. Moreover, preliminary results suggest that disorder specific programs are successful in reducing symptom severity of non-targeted disorders (Titov et al, 2009b).

We have recently completed an RCT pilot study of an Internet-based treatment transdiagnostic treatment for anxiety disorders (Titov, Johnston, Robinson & Andrews, in preparation). Attendance throughout the program was roughly equivalent to that of our previous Internet-based disorder specific programs (76%), and preliminary findings support the efficacy of this initiative.

We are interested in further investigating the efficacy of Internet-based treatments for a population of people suffering from at least one of the following disorders: GAD, social phobia or panic disorder (with or without panic disorder). Additionally, we are interested in assessing the level of support required to help people complete the program as independently as possible.

## Rationale for Performing the Study

Many people with anxiety do not access treatment, despite the availability of diagnosis specific and transdiagnostic face-to-face initiatives. Internet-based treatment may be one way of circumventing the barriers to effective mental health care. We have developed Internet based treatment programs for GAD, social phobia, and panic disorder, which have all suggested that this treatment modality is effective. We have recently completed a RCT pilot study of transdiagnostic treatment for anxiety disorders delivered via the web, and preliminary results suggest that the program is effective.

This proposed study will recruit 150 people with GAD, social phobia, or panic disorder and randomly allocate them to one of three groups: (1) Clinician guided internet-based treatment group, (2) Self-guided internet-treatment group, (3) Wait-list control group (who will receive treatment after the treatment groups have completed the program). We will measure changes in symptom level from the beginning of the 10 week program course of treatment and one week after the conclusion of treatment, and at 3 month follow up. Measurement in the control group will be matched to the pre and post treatment assessment. We will also measure adherence to the lessons, homework, satisfaction with the clinician's input and satisfaction with the mode of treatment generally.

This proposed project employs the same research design as that previously approved by St Vincent's Hospital Human Research Ethics Committee (09/021). However, one additional questionnaire has been added for assessing general anxiety (Depression, Anxiety, Stress Scale, DASS-21, Lovibond & Lovibond, 1995), two questionnaires for diagnosis specific measures of anxiety (Social Phobia Screening Questionnaire, SPSQ, Furmark et al, 1999; Panic Disorder Severity Scale-Self Rating, PDSS-SR, Houck et al, 2002) and two questionnaires for associated variables (NEO-FFI, Costa & McCrae, 1992; Locus of Control Behaviour, Craig et al., 1984).

# STUDY OBJECTIVES

## Primary Objectives

The primary objectives of the study is comprised of three hypotheses: 1) That participants in treatment groups 1 and 2 would show significant improvement on a general measure of anxiety (DASS-21) and on disorder specific measures (GAD-7, PSWQ, SPSQ, PDSS-SR) relative to Controls; 2) that participants in treatment groups 1 and 2 with primary diagnoses of GAD, panic, or social phobia would show significant improvement on relevant disorder specific measures (GAD-7, PSWQ, SPSQ, PDSS-SR) relative to controls with the same primary diagnoses; and 3) that treatment groups 1 and 2 will be equivalent regarding generic and diagnosis specific measures of anxiety.

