## Randomization procedure

The website [www.random.org](http://www.random.org) will be used to determine a list of randomly generated numbers that correspond to a group (Group 1, 2 or waitlist control). Participants will be randomly allocated to one of these groups before completing the brief telephone interview.

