11.4 Randomisation sheet

Randomisation will occur via a true randomisation process ([www.random.org](http://www.random.org)). This list will be generated prior to commencement of the study.

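### Hypothesis 2 makes within-diagnosis comparisons primary, but the stated 80% power has no basis within a diagnosis, where about 17 people per arm give roughly 39% to 65% in the better-powered contrast

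*Protocol*

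**What the plan says.** Section 2.1 (Primary Objectives) opens: "The primary objectives of the study is comprised of three hypotheses". It does not rank them. The second hypothesis is that treated participants "with primary diagnoses of GAD, panic, or social phobia would show significant improvement on relevant disorder specific measures", and the comparison is made "relative to controls with the same primary diagnoses". It therefore calls for a significant result within each of three diagnostic groups.

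Eligibility in the Summary is a single line covering all three: "Meets criteria for GAD, social phobia, or panic disorder (with or without agoraphobia) as a primary diagnosis". No quota, minimum or expected mix is given. Section 3.3 fixes the numbers: "150 in total: CaCCBT: n=50; CCBT: n = 50; Waitlist: n= 50".

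Section 8.1 expects CaCCBT to exceed CCBT by an ES of 0.3 and waitlist by 0.6, then states: "Sample size is powered to have an 80% chance of detecting differences at p<.05". Both effect sizes are between whole groups. Section 8.2 plans ANCOVA with the baseline score as covariate.

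Section 5.7 describes one random.org list assigning numbers to the three groups, and section 11.4 adds: "This list will be generated prior to commencement of the study". No stratification factor is named. Sections 5.6 and 5.7 place allocation before the telephone interview, while section 5.2 has the diagnosis confirmed by telephone with the MINI.

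**The concern.** A primary hypothesis should be one that the trial can reasonably be expected to answer. The sample size is set for arms of 50, but Hypothesis 2 is tested on roughly a third of each arm, three times over. Nothing in section 8.1 exempts it from the power statement, so a reader would assume that a non-significant result in, say, panic disorder is informative.

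What is at stake is the transdiagnostic question itself. Three underpowered primary tests will often give a mixed pattern even when the effect is the same in every diagnosis, and that pattern could be reported as the programme working for one disorder and not another.

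**Working it through.** **Inputs from the protocol.** 50 per arm (3.3); three diagnoses (Summary); ES 0.6 for CaCCBT against waitlist and 0.3 for CaCCBT against CCBT (8.1); 80% power at 0.05 (8.1); baseline-adjusted analysis (8.2). By subtraction, CCBT against waitlist is 0.6 − 0.3 = 0.3. If the two active arms are pooled, the average effect is (0.6 + 0.3)/2 = 0.45.

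**Assumptions.** Two-sided test (sidedness is not stated). Equal thirds, so 50/3 = 16.7 per arm per diagnosis. Baseline-to-post correlation r = 0.5 to 0.7, with effect sizes in raw SD units.

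**Method.** Power of a two-sample t test with noncentrality δ = ES × √[n₁n₂/(n₁+n₂)] on n₁+n₂−2 degrees of freedom. For ANCOVA, ES is replaced by ES/√(1−r²).

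**1. The plan's own figure.** Whole arms of 50, unadjusted:
- ES 0.6: δ = 0.6 × √25 = 3.0, power 84%. This contrast is covered.
- ES 0.3: δ = 1.5, power 32%. The 80% is not reproduced for this contrast, which is a separate matter from Hypothesis 2.

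**2. Within one diagnosis, CaCCBT against waitlist, ES 0.6, 16.7 per arm.** √(16.7/2) = 2.887.

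| r | ES/√(1−r²) | δ | Power |
|---|---|---|---|
| unadjusted | 0.60 | 1.73 | 39% |
| 0.5 | 0.69 | 2.00 | 49% |
| 0.6 | 0.75 | 2.17 | 56% |
| 0.7 | 0.84 | 2.43 | 65% |

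**3. CCBT against waitlist, ES 0.3.** Unadjusted δ = 0.87, power 13%. At r = 0.6, δ = 0.375 × 2.887 = 1.08, power 18%.

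**4. Active arms pooled, 33.3 against 16.7.** √(33.3 × 16.7/50) = 3.33.
- ES 0.45: δ = 1.50, power 31%. At r = 0.6, δ = 1.875, power 45%.
- ES 0.6 in both arms: 50% unadjusted, 69% at r = 0.6, 78% at r = 0.7. This contradicts the protocol's own gap of 0.3 between the arms.

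**5. What could be detected.** With 16.7 per arm, the ES with 80% power is about 1.0 unadjusted. Multiplying by √(1−r²) gives 0.87 at r = 0.5 and 0.71 at r = 0.7. Conversely, 80% power at ES 0.6 unadjusted needs 45 per arm within each diagnosis by the t test, so 3 × 45 = 135 per arm against the planned 50.

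**6. Unequal mix, ES 0.6, unadjusted.** 25 per arm: 55%. 12.5 per arm: 30%. 10 per arm: 25%.

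**7. Pattern across the three diagnoses.** Assume a true ES of 0.6 in every diagnosis, CaCCBT against waitlist, with separate tests in separate people. The chance that all three are significant is 0.39³ = 6% unadjusted, 0.555³ = 17% at r = 0.6 and 0.652³ = 28% at r = 0.7. At least one non-significant result therefore occurs in 94%, 83% and 72% of trials. A mixed pattern (one or two of three significant) has probability 1 − p³ − (1−p)³, which is 1 − 0.059 − 0.227 = 71% unadjusted and 1 − 0.171 − 0.088 = 74% at r = 0.6.

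**The case against.** **The planned ANCOVA is more powerful than an unadjusted test.** This stands. A reader might infer that an effect of the assumed size would be missed in most subgroups. The documents do not support that for CaCCBT: with the planned adjustment at r = 0.6, power is 56%, so a single diagnosis is detected more often than missed. What remains is that no two-arm variant in the range tried reaches 80%, and CCBT stays far below it.

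**Section 8.1 never claimed 80% within a diagnosis.** This also stands. Its effect sizes are between whole groups. The fair criticism is that Hypothesis 2 has no sample-size basis although it is primary, not that the power was computed for it and came out wrong.

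**The effect on the relevant scale may be larger within a diagnosis.** Possibly, and the background reports effect sizes of 1.0 to 1.3 in earlier disorder-specific studies. Those are described as improvement within the intervention groups, and section 8.1 itself separates a pre-post gain of 1.0 from a between-group 0.6. The protocol offers no larger between-group figure for a single diagnosis.

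**The unstratified list is the cause.** A reader might infer this, but low power comes from the number of people. In simulation with 50 people in each diagnosis, average power at ES 0.6 was 37.9% under simple randomisation against 39.0% with exactly balanced cells, so stratifying gains about one percentage point. Any probability of an especially small cell depends on an assumed mix, because no quota exists. Nor is stratification wholly ruled out as sequenced. It cannot use MINI-confirmed diagnosis, but a provisional stratum from self-identified disorder and screening answers is possible. Baseline adjustment also absorbs part of any noise from diagnostic imbalance.

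**Model details may sit in an analysis plan not shown.** True of the model terms. The primary status of Hypothesis 2, the sample size and the power statement are fixed in the protocol.

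**Conclusion.** The point holds: the trial has no demonstrated power for one of its three primary hypotheses. Under equal thirds and a two-sided 0.05 test, power per diagnosis is about 39% to 65% for CaCCBT against waitlist at ES 0.6 (unadjusted, up to r = 0.7). It is 13% to 18% for CCBT at the implied 0.3 and 31% to 45% for the pooled arms at the implied 0.45 (both unadjusted, up to r = 0.6). The mix and r are assumptions. An uneven mix helps the commonest diagnosis at the expense of the rarest. Failure to reach significance in one or more diagnoses is likely even with a common effect, and should not be read as the programme failing for that diagnosis. The overall CaCCBT-waitlist comparison is not affected (84%), so this should be corrected but does not undermine the trial as a whole.

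**What to change.** 1. In section 8.1, state that the 80% power does not apply to Hypothesis 2.
2. In section 2, move Hypothesis 2 to the secondary objectives and word it as estimation: diagnosis-specific effects with 95% confidence intervals from one model with a group-by-diagnosis term, in place of three separate significance tests. With 16.7 per arm, the interval half-width is about 1.96 × √(2/16.7) = 0.68 SD unadjusted, or 0.8 × 0.68 = 0.54 SD at r = 0.6. Stating this in advance would set expectations.
3. Include primary diagnosis, which is already collected, in the models.
4. As a supporting change, allocate after the MINI from separate random.org lists per primary diagnosis, in permuted blocks of varying size. This balances the cells but does not restore power.

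The cost is wording, one fewer primary claim, three lists instead of one, and a change in the order of allocation and interview. Blocking makes allocation slightly more predictable, which varying the block size limits. No extra participants are needed.

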## Investigation plan

A CONSORT-R compliant, registered RCT of the intervention (CaCCBT) versus CCBT versus waitlist control group. This will demonstrate whether the benefit from the CaCCBT intervention is superior to natural remission and placebo response. Because of low adherence to CCBT we think that it is a proxy for a placebo treatment. As in any RCT accurate patient selection, good randomization, reliable and valid outcome measures, and low drop-out rates are critical. Analyses based on completers and on intention to treat will be performed.

There are already over 1000 people on the waitlist for Virtual Clinic. In addition, some media attention is expected to generate more publicity to attract people to the program. The study will be described on the intake website, [www.virtualclinic.org.au](http://www.virtualclinic.org.au). People will read the information about the studies and elect to continue or not. If they choose to apply for the study they will complete an automated screening questionnaire. Only people whose responses to the questions meet selection criteria and undergo a brief phone interview explaining the program will read the information sheet and return an electronic consent form and mail that to the investigators. This will trigger the phone interview in which the diagnosis will be confirmed using the Mini International Neuropsychiatric Interview Version 5.0.0 (Appendix A). Questions about the study will be answered and an offer of treatment made.

Patients will be randomly allocated to CaCCBT group (n=50), CCBT group (n=50), or the waitlist group (n=50). Randomization will be done via [www.random.org](http://www.random.org) (see appendix A).

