**Lesson Eight:**

- **Revise the skills you have learnt.**
- **Make a plan for staying well in the future.**

Participants in the CaCCBT group will receive regular email contact with their clinician, and will be encouraged to carry out homework activities.The patients in the CCBT groups will have same access to the lessons, and homework activities as the CaCCBT groups. Unlike the CaCCBT groups, the CCBT groups will have no clinician contact over the 10 week period, but will receive weekly telephone reminders from administrative staff. The waitlist group will not receive any treatment during this period.

After the treatment group has finished the program, all participants will complete a third set of diagnostic questionnaires. The waitlist group, and any CCBT participants wishing to complete the program with clinician contact, will be offered additional treatment after this.

Effectiveness of the CaCCBT program for anxiety will be measured by comparing waitlist and CCCBT and CaCCBT groups on their pre- and post- treatment scores. Long-term follow up data will compare the CaCCBT and CCBT groups at 3 month follow up.

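### The protocol states three incompatible expectations for CaCCBT versus CCBT, and the difference tests it names cannot support the equivalence claimed in Hypothesis 3

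*Protocol*

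**What the plan says.** Four parts of the Protocol bear on the comparison of clinician-assisted (CaCCBT, group 1) with self-guided (CCBT, group 2) treatment.

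- **Section 2.1, Primary Objectives.** Hypothesis 3 is "that treatment groups 1 and 2 will be equivalent regarding generic and diagnosis specific measures of anxiety". Hypothesis 1, in the same section, expects both treatment groups to improve relative to waitlist.
- **Section 8.1, Sample Size Calculation.** CaCCBT is expected to "improve more than the CCBT group by an ES of 0.3 and waitlist group by an ES of 0.6", and "Sample size is powered to have an 80% chance of detecting differences at p<.05".
- **Section 5.2, Investigation plan.** "Because of low adherence to CCBT we think that it is a proxy for a placebo treatment". The sentence before it says the trial will show whether the benefit of CaCCBT exceeds natural remission and placebo response. Later in 5.2, after the lesson list, the arm is described: "The patients in the CCBT groups will have same access to the lessons, and homework activities as the CaCCBT groups", with weekly reminder calls from administrative staff and no clinician contact.
- **Summary and section 8.2, Analysis Plan.** Both name ANCOVA adjusting for the baseline score. In 8.2, "the between subjects factor compares improvement scores between treatment groups". The document contains no equivalence margin, equivalence test or interval rule.

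**The concern.** The same contrast is predicted to be equivalent, predicted to be 0.3 SD and worth detecting, and used as a comparison with something close to placebo. One result then carries opposite meanings. If the arms finish alike, section 2.1 counts a primary hypothesis as supported, while section 5.2 implies that CaCCBT did no better than its placebo proxy. If CaCCBT wins by 0.3, section 8.1 is borne out and Hypothesis 3 is put in doubt.

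The named analysis adds to the difficulty. A difference test can reject equality or fail to reject it, and failing to reject is not evidence of equivalence, least of all when power is low. The background (section 1.1) gives the level of support that people need as one of the study's interests, so a conclusion about clinician input could rest on lack of precision.

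**Working it through.** **Inputs.** 50 per arm (section 3.3). Expected differences of 0.3 (CaCCBT minus CCBT) and 0.6 (CaCCBT minus waitlist), power 80%, p<.05 (section 8.1). Effects are standardised, so SD = 1. Two-sided testing is assumed, because sidedness is not stated. The baseline-outcome correlation ρ is not given, so 0 (unadjusted), 0.3, 0.6 and 0.8 are shown.

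**1. The plan's own figure.** n per arm = 2(1.960 + 0.842)²/d².
- d = 0.6: 2 × 7.849/0.36 = 43.6, so 44. At 50 per arm, power is about 85%.
- d = 0.3: 2 × 7.849/0.09 = 174.4, so 175. At 50 per arm, power is about 32%.

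Fifty per arm is therefore enough for the waitlist contrast before dropout, but does not give 80% power for CaCCBT versus CCBT. One-sided testing at 0.05 would still need 138 per arm (power 44%). Baseline adjustment would need ρ of about 0.84 to reach 80% two-sided.

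**2. The implied CCBT effect.** 0.6 − 0.3 = 0.3 over waitlist. Section 8.1 thus agrees with Hypothesis 1 that CCBT has an advantage over waitlist, and puts it at half that of CaCCBT.

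**3. What 50 per arm can show on CaCCBT versus CCBT.**
- SE = √(1 − ρ²) × √(2/50) = 0.20 × √(1 − ρ²).
- Non-significance at a true difference of 0.3 is one minus the two-sided 0.05 t-test power (noncentral t).
- The 90% half-width is t(0.95) × SE.
- Power of two one-sided tests (TOST), margin m, true difference 0: 2Φ(m/SE − 1.645) − 1, floored at 0.

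| ρ (assumed) | SE | Non-significant at 0.3 | 90% half-width (SD) | TOST power, m = 0.3 | TOST power, m = 0.5 |
|---|---|---|---|---|---|
| 0 | 0.200 | 68% | 0.33 | 0% | 61% |
| 0.3 | 0.191 | 66% | 0.32 | 0% | 67% |
| 0.6 | 0.160 | 54% | 0.27 | 18% | 86% |
| 0.8 | 0.120 | 30% | 0.20 | 61% | 99% |

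The TOST columns use the normal approximation; t-based values are about one point lower in most cells. If the true difference is 0.3 rather than 0, unadjusted TOST power at a margin of 0.5 is Φ(0.2/0.20 − 1.645) − Φ(−0.8/0.20 + 1.645) = 0.26 − 0.01 = 25%.

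**4. Dropout.** No allowance is stated. If 20% were lost (an assumption; section 1.1 reports adherence of 75% to 88% in earlier programs), 40 per arm would remain, and the 90% half-width at ρ = 0.6 would rise from 0.27 to about 0.30 SD.

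**The case against.** The strongest reply has four parts.

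- **The margin and the equivalence test may be in a separate analysis plan.** That is fair, and their absence alone would not be a point. But the objective, the design rationale and the basis of the sample size are protocol content. A later plan cannot make sections 2.1, 5.2 and 8.1 agree.
- **Nothing says that a non-significant result will be read as equivalence.** Correct. A reader might infer it because no other route is named, but it remains an inference. Nor does the protocol show that its authors believe Hypothesis 3 to be false. A true difference of 0.3 contradicts equivalence only if the margin is 0.3 or smaller, and no margin is given. What can be said is that section 8.1 treats 0.3 as a difference to detect.
- **The planned analysis adjusts for baseline, so unadjusted figures are the pessimistic end.** This stands, and is why a range is shown. A reader might conclude from the unadjusted half-width of 0.33 SD that 50 per arm could never meet a margin of that size or less. The table shows otherwise: with ρ = 0.8, a margin of 0.3 is met about 60% of the time when the true difference is 0.
- **The placebo remark is a stated opinion with a reason.** Section 5.2 gives low adherence as the reason and says the trial will show whether CaCCBT is superior, not that it must be. Beating a waitlist does not by itself rule out a placebo role. So the text does not prove that CCBT cannot serve as a proxy. It does show that the label fits poorly with an arm that receives the same lessons and homework plus weekly calls and is listed as a treatment group.

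**Conclusion.** The point holds as an internal contradiction about a primary hypothesis, together with a stated analysis that cannot support that hypothesis. The contradiction needs no numerical assumption. Its practical size does: under the protocol's own 0.3 difference, the CaCCBT versus CCBT test would miss significance about 68% of the time unadjusted and 66% to 30% of the time for correlations of 0.3 to 0.8. The 90% half-width is 0.33 SD unadjusted and 0.32 to 0.20 SD over the same range. These figures assume 50 analysed per arm, SD 1, two-sided 0.05 and no dropout. A null result on this contrast would be quite likely even if the sample-size section is right, and would say little about equivalence. This should be corrected because it governs how a primary result is read.

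**What to change.** 1. Make sections 2.1, 5.2 and 8.1 state one expectation for CaCCBT versus CCBT.
2. Replace Hypothesis 3 with, for example: *The CaCCBT minus CCBT difference will be estimated with a 95% confidence interval on each of the DASS-21 and the named disorder-specific measures. A non-significant difference will not be reported as equivalence.* The disorder-specific measures should be listed by name.
3. If an equivalence claim is kept, add: *Equivalence will be claimed only if the 90% confidence interval (two one-sided tests) lies wholly within a margin justified on clinical grounds and fixed before any outcome data are seen.* Fixing the margin only before data lock would be too late, because the study is unblinded (section 7) and investigators have access to identifiable data throughout (section 9). State the power that 50 per arm gives for the chosen margin over a range of baseline correlations. At a true difference of 0 and correlations of 0 to 0.8, this is about 0% to 60% for a margin of 0.3 and about 60% to 99% for a margin of 0.5.
4. Reconcile the placebo-proxy wording in section 5.2 with the description of CCBT as a treatment arm.

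The cost is wording and a few more confidence intervals. The sponsor gives up an easy equivalence claim. No change to sample size is needed for the estimation version; keeping equivalence may require one, depending on the margin.
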